## Protocol summary

**Background:** The majority of maternal deaths occur in low-resource countries such as Ethiopia. Maternity waiting homes (MWHs) can be used as an approach to improve maternal health outcomes by bringing women living in underserved locations to obstetric facilities. However, the use of MWHs in Ethiopia is low. Therefore, it is important to investigate strategies that can effectively improve MWH use in rural Ethiopia.

**Methods:** This study will assess the effectiveness of health education provided to couples on the uptake of MWHs among eligible pregnant women in rural Ethiopia. The couples knowledge and attitude towards MWHs will be assessed as well. Cluster-randomized controlled trials will be the study design. The trial will have intervention and control arms. Randomization occurs at the cluster level. Kebeles are clusters. There will be a total of 16 clusters divided into 8 intervention and 8 control clusters. The outcome assessors will be masked. The trial sample size will be 320 couples (160 in each arm). The intervention will be performed for six months. The content of the intervention will be group health education, take-home print health messages, and individual home visits. Health education will be delivered to the intervention group at baseline, and specific leaflets will be provided. Home visits will be conducted two times (i.e., at 3rd and 5th months of the intervention period). The control group will receive the standard care. Baseline and end line data will be collected. An intention to treat approach will be considered. The Chi-square test will be used to assess the statistical difference between the groups, and the difference-in-differences model will be used to measure the effectiveness of the intervention. Furthermore, generalized linear model regressions will be used to estimate the odds of outcomes between the intervention and control groups. The SPSS and/or STATA software will be used to perform the data analysis.

**Discussion:** The study findings can inform the policymakers and healthcare practitioners to use the intervention modality to improve women's access to maternal health services including MWHs maternity waiting home use among pregnant women with limited access to maternal health services in rural Ethiopia and elsewhere.

**Budget:** The total estimated cost of the study is 222,768 ETB (equivalent to \$4,588 USD).

**Trial registration number:** ClinicalTrials.gov Identifier: NCT05015023, date of first registration 20/08/2021.

**Keywords:** maternity waiting home; health education, couples, pregnant women

## Introduction

The sustainable development goals target 3.1 aims to reduce the global maternal mortality ratio to less than 70 per 100,000 live births by 2030. Estimates for 2017 show that some 810 women die every day from pregnancy- or childbirth-related complications around the world. The estimate further declared that 295, 000 women died during and following pregnancy and childbirth, globally. Consequently, the global maternal mortality ratio in 2017 is estimated at 211 maternal deaths per 100,000 live births which is still far from the sustainable development goals target. The majority (94%) of this was reported to be occurred in low-resource settings.

Sub-Saharan Africa (SSA) and Southern Asia accounted for approximately 86% (254,000) of the estimated global maternal deaths in 2017. The SSA alone accounted for roughly two-thirds of maternal deaths and the maternal mortality ratio for Ethiopia is estimated to be 401 per 100,000 live births for the same year. This is more than four-fold higher than the global target. Most maternal deaths are preventable. All women need access to high quality care in pregnancy, and during and after childbirth. It is particularly important that all births are attended by skilled health professionals, as timely management and treatment can make the difference between life and death for the mother as well as for the newborn.

Delays in accessing health care has been identified as the primary cause of maternal mortality, and this is usually attributed to the long distances that women must travel to reach health facilities. MWHs have been identified as an approach to improve maternal health outcomes by bringing women living in geographically isolated and underserved areas closer to a healthcare facility that provides emergency obstetric care. MWHs are lodgings located near healthcare facilities where women can await their delivery date and be transferred to health facility shortly before delivery, or earlier should complications arise. MWHs have been implemented in Ethiopia over the last three decades. However, studies have shown that MWH utilization is low in Ethiopia.

The World Health Organization conditionally recommended that the quality of evidence on the utilization of MWHs be poor and insufficiently documented, and further recommends additional research on “what strategies could be effective” in increasing the utilization of MWHs and improving other key maternal health outcomes. Moreover, studies have shown that women’s use

of MWHs largely depends on their husbands' decisions. Therefore, this study is designed to evaluate the effectiveness of educating couples on MWH use in rural southern Ethiopia.

## **Methods and materials**

### **Objectives**

#### **General Objective**

- ✚ To examine the effectiveness of couple-based health education on utilization of MWHs in rural Ethiopia: a cluster randomized controlled trial

#### **Specific Objectives**

- ✚ To assess the effect of couple-based health education on male-partners knowledge and attitude towards MWHs in rural Ethiopia.
- ✚ To assess the effect of couple-based health education on maternal knowledge and attitude towards MWHs in rural Ethiopia.
- ✚ To evaluate the effectiveness of couple-based health education in improving utilization of MWHs in rural Ethiopia.

### **Study design**

We will use parallel arms cluster-randomized controlled trial design to examine the effectiveness of couple-based health education improving couples knowledge, attitudes and maternal use of MWHs in rural Ethiopia.

### **Study setting**

The research will be conducted in Hadiya Zone of southern Ethiopia. Hadiya Zone is a second-order administrative division located in Southern Nations Nationalities and Peoples Regional State. It is divided into 4 town administrations and 13 rural districts with a total of 359 clusters or Kebeles' (the smallest administrative units). The livelihood of the population mainly depends on agriculture. There are 4 hospitals, 61 health centers, 317 health posts, and 30 MWHs in the Zone. The total population is around 1.2 million of which 619,170 are women. In 2022, about 60,304 women are estimated to be pregnant. For this study, we will select the districts most appropriate for the intervention based on the availability of the MWHs in the districts. Then clusters and participants will be recruited from those districts.

## Sample size calculations

The Hooper and Bourke method for cluster randomization studies of parallel arms with repeated cross-sections is used to calculate the sample size. To illustrate within intraclass correlation coefficient (ICC) and between ICC, the technique comprises the measurement of two design effects, with the product of the two being used to inflate the sample size for individual randomization. The within ICC is the correlation between any two pregnant women in the same cluster, while the between ICC is the correlation between any two pregnant women in different clusters. The first design effect ( $d_c$ ) attributable to cluster randomization is measured using a within ICC of 0.05 obtained from a community-based cluster randomized trial in Ethiopia. The design effect ( $d_c$ ) is calculated as:

$$d_c = 1 + (m - 1)\rho$$

Where  $m$  is the cluster size assumed to be 20 (i.e., the total number of pregnant women who will be questioned in each cluster) and  $\rho$  is the within ICC.

The second design effect ( $d_r$ ) attributable to repeated evaluations (baseline/endline) is calculated by using the within ICC and a cluster autocorrelation coefficient ( $\pi$ ) of 0.80.

The second design effect ( $d_r$ ) is calculated as:

$$d_r = (1 - r^2)$$

Where  $r = \left( \frac{m\rho\pi}{d_c} \right)$

The required sample size is then calculated by multiplying the ‘sample size assuming individual randomization’ by both design effects ( $d_c$  &  $d_r$ ). It is calculated as:

$$n = \left[ \frac{(a+b)^2 * (p_1 q_1 + p_2 q_2)}{(p_1 - p_2)^2} \right] * d_c d_r$$

Where:

$n$  represents the sample size in each of the arms i.e., intervention and control

$a$  represents conventional multiplier (1.96) for alpha ( $\alpha = 0.05$ ) and  $b$  represents conventional multiplier (0.842) for power ( $1 - \beta = 0.80$ )

$p_1$  represents proportion of post-intervention users of MWH and  $q_1$  represents proportion of post-intervention non-users of MWH.

$p_2$  represents proportion (50%) of users of MWH taken from a study in Gurage Zone, Southwest Ethiopia  and  $q_2$  represents pre-intervention proportion of non-users of MWH.

$|p_1 - p_2|$  *an effect size* - is an absolute change in proportion of MWH utilization after intervention. It is estimated to be 20%.

In addition, the following parameters are considered: 95% CI, 80% power, 1:1 allocation ratio of intervention to control, 10% potential loss to follow up, and tabulated sample size ( $n_0 = 199$ ) required to detect a difference in two proportions at 5% significance level with 80% power in literature.  According to Hooper and Bourke, the number of clusters (K) for the sample is determined using the formula  $K = (n_0 d_c d_r) / m$ . The final sample size is calculated by substituting the specified values into the above formula. Hence, a total of 16 clusters are needed, with an approximated final sample size of 320 couples. The two arms each will have 160 couples (pregnant women with their male partners).

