### Sampling procedure

Sixteen clusters will be selected based on MWH availability in the area. These clusters will be randomly assigned to intervention and control groups. Census and/or health post records will be used to identify pregnant women in the chosen clusters, resulting in the formation of a sampling frame. The study participants will then be selected using a simple random sampling technique from the sampling frame. Each cluster will have 20 couples (20 wife-husband pairs). The same sample of participants assessed at baseline will be assessed at end line to measure the outcome (Figure 2).

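### The 80% power for 16 Kebeles rests on large-sample multipliers and a repeated-cross-section design effect; with 8 clusters per arm and a re-interviewed cohort it needs restating as a conditional figure

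*Protocol*

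**What the plan says.** All of the following is in the Protocol.

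- **Multipliers** (Sample size calculations): the formula "represents conventional multiplier (1.96) for alpha" 0.05 and "represents conventional multiplier (0.842) for power" of 0.80. These are standard normal quantiles.
- **Proportions**: p2 "represents proportion (50%) of users of MWH taken from a study in Gurage Zone, Southwest Ethiopia". Of the absolute change after intervention the text says "It is estimated to be 20"%.
- **Clustering**: the first design effect "is measured using a within ICC of 0.05 obtained from a community-based cluster randomized trial in Ethiopia", with 20 women per cluster. The second uses a cluster autocorrelation of 0.80. The method is named as one for parallel arms with repeated cross-sections.
- **Number of clusters**: a tabulated n0 = 199, described as "required to detect a difference in two proportions at 5% significance level with 80% power in literature", enters K = n0·d_c·d_r/m. A 10% loss to follow-up is listed among the parameters, but no step shows where it is applied. The section ends: "Hence, a total of 16 clusters are needed, with an approximated final sample size of 320 couples".
- **Follow-up** (Sampling procedure): "The same sample of participants assessed at baseline will be assessed at end line to measure the outcome".
- **Estimator** (Primary outcome; Statistical analysis): the effect is measured by difference-in-differences. The text does not say whether this is a change score or a baseline-adjusted model.

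**The concern.** The stated power depends on three choices that do not fit the trial described elsewhere in the protocol.

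1. **Quantiles.** 1.96 and 0.842 suit a comparison with many independent units. With 8 Kebeles per arm, a cluster-level comparison has 2 × (8 − 1) = 14 degrees of freedom and a critical value of 2.145.
2. **Design.** The second design effect is for different women at each survey, but the protocol re-interviews the same couples. The correlation of a woman's own two responses is left out.
3. **Estimator.** The factor 1 − r² describes an analysis that adjusts for baseline. The protocol names difference-in-differences, which as a plain change score has a different and less favourable factor.

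In addition, the formula defines n as per arm, while n0 = 199 carries no such label and is not tied to the 10% loss.

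Stated power is part of how a null result will be read, and a reader cannot tell from the text which design and analysis the 80% refers to.

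**Working it through.** **Inputs from the protocol:** p2 = 0.50, p1 = 0.70, ICC ρ = 0.05, m = 20, cluster autocorrelation π = 0.80, 8 Kebeles per arm, 10% loss (20 becomes 18 per Kebele). **Assumed, because the protocol gives no value:** individual autocorrelation s, the within-woman correlation between surveys apart from the cluster effect, from 0 to 0.5.

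**1. The protocol's own figure**

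- d_c = 1 + 19 × 0.05 = 1.95
- r = 20 × 0.05 × 0.80 / 1.95 = 0.410
- d_r = 1 − 0.410² = 0.832
- d_c·d_r = 1.622
- K = 199 × 1.622 / 20 = 16.14, taken as 16 (322.7 couples, stated as about 320)

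The figure reproduces.

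**2. What n0 = 199 can mean**

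The protocol's formula before design effects gives (1.96 + 0.842)² × (0.21 + 0.25) / 0.20² = 90.3 per arm, or 180.6 in total.

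| Reading of 199 | Total clusters |
|---|---|
| Two-arm total, already inflated by 10% (180.6 × 1.1 = 198.6) | 16.14 |
| Two-arm total before loss: 199/0.9 × 1.622/20 | 17.9 |
| Per arm: 2 × 16.14 | 32.3 |

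Only the first supports 16. It also agrees with the per-arm route: 90.3 × 1.622 = 146.4, and 146.4 × 1.1 = 161, against 160 stated.

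**3. Power at the protocol's inputs, baseline-adjusted, s = 0**

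Effective n per arm = 8m / (d_c·d_r); SE = √(0.46 / effective n); noncentrality = 0.20 / SE. Power is taken first from the normal distribution with 1.96, then from the noncentral t with 14 df and 2.145.

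| | m = 20 (no loss) | m = 18 (10% loss) |
|---|---|---|
| d_c·d_r | 1.95 × 0.832 = 1.622 | 1.85 × 0.849 = 1.570 |
| Effective n per arm | 160/1.622 = 98.7 | 144/1.570 = 91.7 |
| SE | 0.0683 | 0.0708 |
| Noncentrality | 2.93 | 2.82 |
| Power, normal | 83.4% | 80.6% |
| Power, t on 14 df | 77.7% | 74.8% |
| Difference detectable at 80%, 14 df | about 20.5 points | about 21 points |

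**4. Cohort and estimator**

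For a cohort, r = (mρπ + (1 − ρ)s) / d_c. The overall factor is d_c(1 − r²) for a baseline-adjusted analysis and d_c·2(1 − r) for an unadjusted change score. Power on 14 df:

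| Assumed s | Adjusted, m = 20 | Adjusted, m = 18 | Change score, m = 18 |
|---|---|---|---|
| 0 | 77.7% | 74.8% | 59.1% |
| 0.1 | 79.8% | 76.9% | 62.9% |
| 0.2 | 82.2% | 79.3% | 67.0% |
| 0.3 | 84.8% | 82.1% | 71.6% |
| 0.5 | 90.7% | 88.6% | 82.0% |

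The adjusted analysis reaches 80% at s of about 0.11 (m = 20) or 0.22 (m = 18). The change score at m = 18 needs s of about 0.46.

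**5. Rounding**

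At m = 20, normal-quantile power is 83.7% with K = 16.14 and 83.4% with K = 16, a loss of about 0.3 points.

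**The case against.** The strongest reply is that the sample size section does what it says. Its arithmetic reproduces, 16 Kebeles give more than 80% by its own method even after the 10% loss, and the move to 14 degrees of freedom shifts the detectable difference by only 0.5 to about 1 point. For a cohort analysed with baseline adjustment, the repeated-cross-section factor is conservative, and a modest within-woman correlation brings power back to 80%.

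Most of this stands, and it rules out several stronger readings:

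- **That the trial's power is 75%.** That value assumes 10% loss, no within-woman correlation and a baseline-adjusted analysis, and it uses the same repeated-cross-section factor that does not match the cohort. It is one scenario.
- **That the cluster count is an arithmetical error, or that rounding down matters.** Neither holds. The shortfall in step 3 comes from the t quantiles alone.
- **That 32 clusters were needed.** A per-arm reading of 199 conflicts with the stated total of 16 and with the per-arm route to about 161.
- **That 199 is certainly a total including loss.** The match with 198.6 is suggestive, but the protocol calls the figure tabulated and does not say what it covers.

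The reply does not rescue the unconditional 80%. The correlation that would restore it is nowhere in the protocol, and the named estimator, if run as an unadjusted change score, works in the opposite direction.

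**Conclusion.** The concern holds in a conditional form. At the protocol's own inputs, 80% power for a 20-point difference is reached only with normal multipliers that 8 clusters per arm do not support. A baseline-adjusted analysis on 14 degrees of freedom gives about 78% with full retention and 75% after the stated loss, which is 6 points below the normal calculation in each case.

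These figures rest on an ICC of 0.05, a cluster autocorrelation of 0.80, unpooled variances at 50% and 70%, and s = 0. The power of the actual cohort design cannot be fixed from the document. At 18 per Kebele and assumed s from 0 to 0.5, it runs from 75% to 89% with baseline adjustment and from 59% to 82% with an unadjusted change score. The choice of estimator therefore matters more than the choice of quantile.

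The undefined n0 is a separate defect of documentation, since only one of its three readings leads to 16 clusters. The design remains viable; the power statement and its derivation need correcting.

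**What to change.** Keep 16 Kebeles and 320 couples, and rewrite the sample size paragraph:

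1. Replace the unconditional 80% with power computed on 14 degrees of freedom for the closed cohort and the planned estimator, with the 10% loss applied (18 per Kebele).
2. Show that power over a stated range of assumed individual autocorrelations, labelled as assumptions, and give the difference detectable at 80%.
3. Have the sponsor confirm and state what n0 = 199 represents: total or per arm, before or after loss. If it is the two-arm total including 10%, show 180.6 × 1.1.
4. Describe the design as a closed cohort, consistent with the Sampling procedure section.
5. If the 1 − r² factor is kept, specify the difference-in-differences as a baseline-adjusted analysis. If an unadjusted change score is intended, use its own factor, 2(1 − r).

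The cost is one revised paragraph and one clarifying sentence on the estimator, submitted as a protocol amendment. No Kebeles or couples are added. The price is a power statement that is conditional and, at some assumed correlations, less favourable than 80%.

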### **Eligibility criteria**

The study participants will be couples living together where the women are pregnant in the beginning of second trimesters of pregnancy (14-16 weeks of gestation) and had given birth in the last 5 years before the current pregnancy, permanent residents of the study area, living  $\geq 2$  hours of walking distance from the nearest health facility and/or have no or limited access to public transportation, and are willing to participate in the study.

### **Participants' selection**

Hadiya Zone was one of lowest performers in SNNPR regarding MWH use in 2021. This situation drew the attention of the researchers to perform this study in this area. First, health centers with functional MWHs will be identified based on the MWH functionality criteria adopted from national guideline. During the assessment; the availability of staff, beds for sleeping, water supply, kitchen and cooking utensils, bathrooms, and latrines will be considered as crucial to declare the functionality of MWHs.

In Ethiopian health system, one health center serves an estimated 25,000 population with a catchment of five Kebeles (clusters). Each Kebele contributes 5000 population. Secondly, all the Kebeles under each health center catchments will be listed. Thirdly, all non-adjacent Kebeles relatively from the health centers will be identified. Next, 16 non-adjacent Kebeles will be chosen. At least one cluster (Kebele) will be left between non-adjacent Kebeles, and this will serve as a buffer zone.

The selected 16 non-adjacent Kebeles will be randomly assigned to intervention and control groups using simple randomization. Census and/or health post records will be used to identify pregnant women. Then, women will be asked their Last Menstrual Period (LMP) to estimate the gestational age. Women who are in the beginning of second trimesters (14 -16 weeks of gestation) will be listed. This list will be used as a sampling frame. The study participants will be selected from each Kebele using simple random sampling technique.

Participants who consent to involve in the study with their male partners (husbands) will be included in the study. Women and their male partners will be requested to sign an informed consent to ensure voluntary participation. Once consent is obtained, each participant will be interviewed to complete a baseline survey. The baseline questionnaires contain socio-demographic and obstetrics characteristics, health services including MWH use, paternal and maternal knowledge and attitude, and male partner involvement.

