### **Randomization and blinding**

Kebeles' will be the randomization unit whereas the observation or analysis units will be the individual study participants. The selected 16 non-adjacent Kebeles will be listed alphabetically. A restricted randomization with a 1:1 allocation will be used to assign the Kebeles to the intervention or control groups. In Microsoft Excel 2010, a list of random numbers will be created, and the generated values will be fixed by copying them as "values" next to the alphabetic list of the Kebeles. The first eight will be chosen as intervention clusters, and the last eight will be chosen as control clusters, in ascending order based on the produced random numbers. Moreover, a statistician who is blind to the study groups and is not involved in the research will create the allocation sequence and randomize the clusters. The allocation of Kebeles to the intervention or control groups will be hidden from the data collectors or outcome assessors.

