### **Implementation of the intervention**

The intervention will be provided to the couples in the intervention group. Group health education, provision of leaflets (print health messages), and home visits will be conducted. Health education will be provided once in the first month whereas the home visits will be performed two times at two months intervals (i.e., at 3rd and 5th months). Print health messages will be provided three times (i.e., at first contact during health education and at each of the two home visit).

The health education session will be provided in a group for 90-120 minutes. All participants in the intervention within a Kebele will be gathered at one common place and receive health education. Health extension workers and Kebele leaders will select the place of health education and invite the participants. Both women and their male partners will be invited to receive the health education. This will be done in all eight intervention Kebeles, and as a result, eight health education sessions will be performed at baseline.

Health education will address the importance and kinds of paternal support, and purpose and benefits of staying in MWHs. The services available at MWHs, the benefits of staying at MWHs, the right time to visit MWHs, and the importance of paternal support will be discussed. Types of paternal support during pregnancy and MWH stay, such as allowing a spouse to stay at MWH, accompanying her to MWH, providing financial support during MWH stays, providing food and other necessary materials, looking after the home, and caring for the remaining children at home,

will be addressed. Health messages in leaflets focus on paternal support and the purpose and advantages of MWHs. Next, the schedule of home visits will be proposed through discussions with participants, with an emphasis that both women and their male partners will be contacted at their residence.

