### **Trial activity schedule**

The eligibility screening, obtaining informed consent, participant allocation, and baseline data collection will be performed in the months of September and October 2022. The actual intervention will be performed from November 2022 to April 2023. Then the endline data collection will be conducted two-weeks after the completion of the intervention, i.e., after May 15, 2023.

Accordingly, the participants' enrollment, intervention, and assessment schedule is summarized as follows (Table 3).

**Table 3:** Schedule of enrolment, interventions, and assessments

|               |                             |                        | STUDY PERIOD                            |                |                |                |                |                |                   |
|---------------|-----------------------------|------------------------|-----------------------------------------|----------------|----------------|----------------|----------------|----------------|-------------------|
|               |                             | Enrolment & Allocation | Post-allocation
(Intervention Phase) |                |                |                |                |                | Close out         |
| Time point    |                             | t (-1)      | t 1                          | t 2 | t 3 | t 4 | t 5 | t 6 | t (+1) |
| Enrolment     | Eligibility screen          |                        |                                         |                |                |                |                |                |                   |
|               | Informed consent            |                        |                                         |                |                |                |                |                |                   |
|               | Allocation                  |                        |                                         |                |                |                |                |                |                   |
| Interventions | Health Education + Leaflets |                        |                                         |                |                |                |                |                |                   |

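### The protocol gives conflicting orders for cluster allocation, consent and baseline, and nowhere withholds the allocation until recruitment and baseline close, so recruitment bias is possible and can be reduced by rewording

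*Protocol*

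**What the plan says.** Three sections of the protocol describe the order of events.

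- **Participants' selection.** The 16 chosen Kebeles are "randomly assigned to intervention and control groups using simple randomization. Census and/or health post records will be used to identify pregnant women". The text then moves to asking the last menstrual period, listing women at 14-16 weeks, drawing a simple random sample, obtaining consent from both partners and, once consent is given, the baseline interview.
- **Sampling procedure.** The order is the same: "These clusters will be randomly assigned to intervention and control groups. Census and/or health post records will be used to identify pregnant women", followed by the sampling frame and the random sample.
- **Trial activity schedule.** The order differs: "The eligibility screening, obtaining informed consent, participant allocation, and baseline data collection will be performed in the months of September and October 2022". Then: "The actual intervention will be performed from November 2022 to April 2023".

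On concealment, Randomization and blinding has a statistician from outside the research randomise the clusters, and says: "The allocation of Kebeles to the intervention or control groups will be hidden from the data collectors or outcome assessors". It mentions no one else. Table 1 names health extension workers as those who give the education session and make the home visits. Ethics approval requires written consent from cluster representatives as well as participants before data collection starts.

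**The concern.** In a cluster trial, randomising the Kebeles makes the clusters comparable. It does not make the enrolled couples comparable if the people who list them, seek their consent or give it already know the arm. Couples inclined towards a maternity waiting home (MWH) might then be listed or agree more readily in intervention Kebeles than in control Kebeles.

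Entry leaves room for this. Gestation rests on recall of the last menstrual period, limited access to transport is a judgement, and both partners must be willing. Baseline knowledge, attitude and earlier MWH use would also be measured after allocation. A difference created at entry would carry into the comparison of MWH use at endline, and an intention-to-treat analysis keeps whoever was enrolled, so it cannot undo it.

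**Working it through.** **1. The stated orders side by side**

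| Section | Order given |
|---|---|
| Participants' selection | assign Kebeles; identify, list and sample women; consent; baseline |
| Sampling procedure | assign Kebeles; build frame; sample women |
| Trial activity schedule | screen; consent; allocate; baseline |

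The first two place assignment before consent; the third places consent before allocation. Where baseline is mentioned, allocation comes before it. The schedule also speaks of "obtaining informed consent, participant allocation, and baseline data collection", although the unit of randomisation is the Kebele, so it is unclear which step is meant. No section has the allocation held back until baseline closes.

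**2. What each safeguard covers**

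- *Masking.* It covers data collectors or outcome assessors. The protocol does not name those who list, screen and consent, and does not mention extension workers, Kebele leaders or couples. If cluster representatives consent after assignment, that is another point at which the arm could become known locally.
- *Simple random sampling.* It limits choosing among listed women. It acts after the list is made and before consent, so it guards neither step.
- *Difference-in-differences.* Suppose selection raises underlying MWH use in the intervention arm by b, and a share s of that rise shows in the baseline measure. The remaining bias is (1 - s) x b. Women enter at 14-16 weeks, while the protocol's definition of an MWH puts the stay in the final 2-3 weeks. Baseline use must therefore refer to an earlier pregnancy. Motivation specific to this pregnancy need not show there, so s = 1 cannot be assumed.

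**3. The design figure, and whether the fix moves it**

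Inputs from Sample size calculations: m = 20, within ICC 0.05, cluster autocorrelation 0.80, p2 = 0.50, difference 0.20 (p1 taken as 0.70), multipliers 1.96 and 0.842, tabulated n0 = 199.

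- d_c = 1 + 19 x 0.05 = 1.95
- r = 20 x 0.05 x 0.80 / 1.95 = 0.410; d_r = 1 - 0.410² = 0.832
- d_c x d_r = 1.622
- Individual n = (1.96 + 0.842)² x (0.21 + 0.25) / 0.20² = 90.3 per arm, 180.6 in total; x 1.1 for loss = 198.6, matching 199
- 199 x 1.622 = 322.7 couples; / 20 = 16.1 clusters

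This reproduces the stated 320 couples in 16 clusters to within rounding. The time of release enters none of these terms, so the fix leaves 16 x 20 = 320 unchanged.

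**4. Illustration only (assumed inputs, not estimates)**

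The protocol has no refusal or selection figures. Suppose that half of the listed couples would use an MWH and that, in the intervention arm only, 95% of would-be users consent against 75% of the others. That arm's underlying use becomes 0.475 / (0.475 + 0.375) = 55.9%, against 50%. With 85% in place of 75% it becomes 0.475 / (0.475 + 0.425) = 52.8%.

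Now take a true null, 144 couples per arm (160 less 10%), an endline comparison and the normal approximation. The standard error is the square root of [p(1 - p) + 0.25] x design effect / 144, where p is 0.50 plus the shift. The two-sided 5% test then rejects as follows:

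| Shift | Design effect 1.622 | Design effect 1.95 |
|---|---|---|
| 0 points | 5% | 5% |
| 2 points | 6% | 6% |
| 5 points | 10% | 9% |
| 10 points | 27% | 23% |

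The factor 1.622 credits the baseline measurement; 1.95 is the clustering factor alone. Both columns let the whole shift pass through (s = 0), so they are upper figures for a difference-in-differences that absorbs part of it.

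**The case against.** The other side has several fair points.

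- **Narrative order is not a timetable.** Participants' selection uses ordering words for choosing the clusters, but none ties assignment to the listing of women. If the activity schedule governs, consent precedes allocation and much of the consent route closes. This stands as a reason for caution, and it is why the point is put as a conflict to be reconciled. Even on that reading, allocation precedes baseline and its release is not controlled.
- **Masked staff may also recruit.** Consent leads straight into the baseline interview, so the masked data collectors plausibly take it. That would close part of the route, but the protocol does not say so, and it would not cover the listing of women or what couples themselves know.
- **The estimator may absorb some of it.** The women all gave birth within five years, so earlier MWH use can be measured and part of a shift subtracted. This stands in part, for the reason given in the working.

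A reader might infer that the intervention deliverers control enrolment, from the sentence "Health extension workers and Kebele leaders will select the place of health education and invite the participants". The document does not support that. The sentence concerns inviting couples already in the intervention arm to the education session. It shows that these people will know the arm by then, and nothing about who recruits.

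A reader might also infer a definite bias, for example one fifth of the target effect: swapping 20% of enrolees for couples with 70% in place of 50% use gives 0.20 x 0.20 = 4 points out of 20. The arithmetic is right, but the swap is assumed, the 70% is simply the planning rate plus the target effect, and full pass-through is assumed as well.

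**Conclusion.** The concern holds as a conflict and a gap in the plan. The sections disagree on the order of allocation and consent. None withholds the allocation until recruitment and baseline close, and the stated masking does not reach everyone who could influence listing or consent. A route for recruitment bias is therefore open in the plan as written.

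Its size cannot be derived from the protocol; the figures in the working show only that modest differential consent could matter against a 20-point target. The conclusion rests on reading the order of the text as the intended order, and on the protocol's silence about who recruits. It does not establish that bias will occur. Nor would later release remove the bias outright: that needs the listers, those taking consent and the couples all to be unaware of the arm until baseline closes.

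**What to change.** Reword Participants' selection, Randomization and blinding, Trial activity schedule and Sampling procedure so that all four give one sequence:

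1. choose the 16 Kebeles;
2. list and sample the women;
3. obtain both partners' consent;
4. finish baseline in all 16 Kebeles;
5. only then have the independent statistician generate or release the allocation.

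State who lists, screens and consents couples, and that they are unaware of the arm.

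The sample size, cluster count and calendar months do not change: September and October 2022 are already set aside for enrolment and baseline, with the intervention from November. The price is that education sessions cannot be arranged by arm until baseline closes, which leaves little slack before November. The protocol does not cost the step itself. The change reduces recruitment bias; it does nothing about differential dropout later on.
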